### Study Intervention

#### Implementation of the Cognitive Training Program

Participants in the cognitive training group will receive 10 weeks of the process-based multi-task cognitive training program with 60 min group training sessions (a small group of six participants) each given three times per week. This cognitive training program consisted of eleven training tasks in total, with a varying degree of overlap between tasks. The tasks are divided into three categories: 1) warm-up exercise; 2) practice in order; and 3) expanding training (**Table 2**). The task of warm-up exercise lasting 10 min, practice in order and expanding training tasks lasting 50 min. All cognitive tasks are completed within a medical university setting supervision of postgraduate in Master of Nursing Specialist. The program ensures that the ratio of a participant-to-researcher is no greater than 6:1 (6 participants per researcher). Each training task for all nursing specialists was randomly assigned. During the training period, the participant will have an identical training schedule. To balance the social-interaction effect, participants in the cognitive training group participated in the same health education program as the wait-list control group. Participants were reminded via smartphone to complete their training program if missing over 2 weeks. Besides, we develop a training paper record form, and the training record can be checked.

**Table 2 T2:** Tasks of process-based multi-task cognitive training program.

Categories	Tasks	Targeted domain	Difficulty levels/rounds	number of hours	A brief description of the tasks
Warm-up exercise	Recall the names	Memory	0/20	10min	Firstly, introduce yourself one by one (i.e., name, age, occupation). Then, inform participants to remember these names. The participants are asked to write down the names of the other five on white paper according to their memory at the end of cognitive training.
	You act I guess	Working memory	0/1		Firstly, participants were divided into three groups of two. Then, one participant facing the audience uses the most accurate body language to express the meaning of words, while other participants with their backs to the audience are asked to guess those words. Each group is limited to 2 min.
Practice in order	Match the cylinders	Executive function	1/64	50min	Firstly, take any set of socket cylinder socket*, make the cylinder out of the socket, placed near the corresponding socket block, then throw the order of a group of cylinders into confusion. The participants will be required to place each cylinder into appropriate holes in a long wooden socket block with the left-to-right or the right-to-left order. There are sixty-four cylinder socket combinations. With more socket cylinders and change in combination model shown, the difficulty level increases.
	Match the socket apertures		2/64		Firstly, take any set of socket cylinder socket, make the cylinder out of the socket, placed near the corresponding socket block, then throw the order of a group of cylinders into confusion. A wooden cylinder was selected and placed it into the participant’s hand. The participants will be required to find the corresponding position of each cylinder and place it into appropriate holes in a long wooden socket block. With more socket cylinders and changes in the combination model shown, the difficulty level increases.
	Locate the cylinders		3/64		Firstly, take any set of socket cylinder socket on the table, make the cylinder out of the socket, placed socket block on another table. The participants will be required to select suitable cylinders that were shown in the first group and place each cylinder into appropriate holes in a long wooden socket block with the left-to-right or the right-to-left order according to their memory. With more socket cylinders and changes in the combination model shown, the difficulty level increases.
Expanding training	Recall the cylinders		4/64		The participants will be required to complete a task on level 1 (Match the cylinders) with eyes closed. With more socket cylinders and changes in the combination model shown, the difficulty level increases.
	Recall and locate the cylinders		5/64		The participants will be required to complete a task on level 2 (Match the socket apertures) with eyes closed. With more socket cylinders and changes in the combination model shown, the difficulty level increases.
	Recall the sequence of the colored cylinders		6/64		Firstly, take any set of socket cylinder socket with colors ** (Brand Name: DAWONMONTESSORI; Model Number: DW 1002). Then the participants will be required to complete a task on level 1 (Match the cylinders). With more socket cylinders and changes in the combination model shown, the difficulty level increases.
	Stereoscopic cylinders training		7/4		Firstly, take any group of cylinder with colors**. Participants were asked to stack two or more cylinders high according to the card. The card consists of nine squares of the same size. Forty cylinders of different colors and diameters are inside the nine square randomly. The cylinder is not evenly distribute in the square. With more number of stacks, the difficulty level increases.
	Hunt for the colors		8/10		Firstly, take any set of socket cylinder socket with colors (red or green, blue, yellow) are shown. Then the participants will be required to complete a task on level 1 (Match the cylinders) according to cylinder color card (the time of observing card should not exceed 60 s). With more socket cylinders and changes in the combination model shown, the difficulty level increases.

*The first set of cylinders increases in depths and widths, the second set of cylinders only increases in depths with the same widths, the third set of cylinders only increases in widths with the same depths and the last set of cylinders increases in widths but decreases in depths.

**The Cylinders are four sets of wooden cylinders, each a different color with varying widths and depths as same as the cylinder blocks.

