The calculation of sample size is based on the change in executive function after 10-week, which is the primary outcome variable in this study. A meta-analysis found that significant benefits of cognitive training are superior to the wait-list and the effect size of executive function training used to calculate the sample size is 0.575 [0.093,1.056] (18, 19). Sample size estimation was conducted using statistical software G*power. In the analysis with an independent t-test using a power of 80% and a type 1 error of 5%, the calculated total sample for this study is 78. Considering a 15% dropout rate and maximum to ensure the credibility of the cognitive training, we will recruit 46 participants in each group. Thus, the total required sample size for this study is 92 participants.

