#### Statistical Considerations

The primary and secondary outcome measures were analyzed using data from the intention-to-treat. Moreover, the protocol set principle was defined as those participants or the participants who completed at least 80% adherence to the program initially formulated and assessments all the required will be included. We will compare the characteristics of the completed participants versus dropout ones. Sensitivity analyses of completed participants will be further performed to explore the potential for dropout participants, and the results will be categorized as bias. Listwise deletion will be adopted to estimate treatment effects and sensitivity of the cluster dropout if missing values satisfy the criteria of the losing data entirely at random; otherwise, multiple imputation data strategies will be adopted.

Data processing and statistical analysis will be conducted using SPSS 21.0 and MatLab (The Mathworks Inc. 2016). Descriptive statistics will be reported as frequencies for categorical variables and means ± standard deviations for continuous variables. The adoption mainly the method of exploratory analysis to examine the distribution state of data. The proportionality of baseline data for both groups is compared by the non-parameters Wilcoxon test, chi-square test, and t-test. Regarding the primary outcome, a repeated ANOVA test will be used to evaluate the differences of changes and long-term effect in outcome measurement index performance in the cognitive training group and the wait-list control group, within-group over time, and interaction effects. The simple effect analysis will be added when there is an interaction between intervention factors and time factors. Secondary outcomes will be analyzed using similar statistical methods. The mediating effect model was used to test the transfer effect of cognitive training on untrained cognitive domains, with cognitive training as the mediator. A significant statistical will be considered as P < 0.05 for all comparisons. The effect size (r) was calculated using Cohen’s d to estimate the between-group effect sizes.

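### Training is given in groups of six, but the sample size and the primary analysis treat participants as independent; if outcomes correlate within groups, the standard error is understated

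*Protocol article*

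**What the plan says.** **Delivery.** Participants are randomised individually 1:1 (Study Procedure). The training arm then attends "group training sessions (a small group of six participants" for 10 weeks, and "the ratio of a participant-to-researcher is no greater than 6:1 (6 participants per researcher" (Implementation of the Cognitive Training Program). Table 2 makes the group part of the warm-up: members introduce themselves and later write down the names of the five others, and one guessing game is played in pairs. Controls attend health education classes whose size is not given (Control Intervention). The training arm follows the same health education programme.

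**Sample size** (Study Design and Participants). "the effect size of executive function training used to calculate the sample size is 0.575 [0.093,1.056", and the calculation begins "In the analysis with an independent t-test", with 80% power and a 5% type I error. It gives a total of 78, raised to 92 (46 per arm) for 15% dropout. No design effect is applied.

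**Analysis** (Statistical Considerations). For the primary outcome, "a repeated ANOVA test will be used to evaluate the differences of changes and long-term effect in outcome measurement index performance". The factors are arm, time and their interaction, and secondary outcomes are to be handled similarly. There is no term for training group or trainer. The one use of the word cluster in that section concerns dropout and missing data, not correlation between outcomes.

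**The concern.** People who train together share peers, sessions and supervision, and their outcomes may therefore be more alike than those of people in different groups. The article itself recognises a social-interaction effect, which it tries to balance with the shared health education.

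A repeated ANOVA accounts for correlation between one person's measurements over time. It does not account for correlation between different people in the same training group. An independent t-test makes the same assumption of independence between people.

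Positive within-group correlation would make the variance of the training-arm mean larger than either method assumes. Intervals would be too narrow and the primary test would reject too often under the null. True power would also be below the stated figure. The inflated rejection rate matters most, because it leans towards a false claim of benefit.

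**Working it through.** **1. Reproduce the plan's own figure.** Inputs: standardised effect 0.575, alpha 5%, power 80%, two-sample t-test (noncentral t).
- One-sided: 39 per arm, total 78. This matches; power at 39 per arm is 80.8%.
- Two-sided: 49 per arm, total 98. This does not match.
- Dropout: 78 / 0.85 = 91.8, so 92; 39 / 0.85 = 45.9, so 46 per arm. Both match.

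The stated total therefore corresponds to a one-sided test, although sidedness is not stated. Power is compared on that basis below.

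**2. Groups and their analysed size.** 46 / 6 = 7.67, so about eight training groups. With 39 of 46 analysed, the mean analysed size is 39 / 7.67 = 5.09.

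**3. Formulas, with clustering in the training arm only.**
- Design effect in the training arm: DE = 1 + (m − 1) × ICC.
- Variance of the difference relative to the independent case: V = (DE + 1) / 2.
- True over naive standard error: r = √V. The naive standard error is √(2/39) = 0.226 SD.
- True type I error of a nominal two-sided 5% test: 2 × [1 − Φ(1.96 / r)].
- One-sided power: noncentral t with effect 0.575 / r at 39 per arm.

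**4. Results with m = 5.09.** The ICC is an assumption; the document gives none.

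| ICC | DE | V | r | Two-sided type I error | One-sided power |
|---|---|---|---|---|---|
| 0 | 1.00 | 1.00 | 1.00 | 5.0% | 81% |
| 0.02 | 1.08 | 1.04 | 1.02 | 5.5% | 79% |
| 0.05 | 1.20 | 1.10 | 1.05 | 6.2% | 77% |
| 0.10 | 1.41 | 1.20 | 1.10 | 7.4% | 74% |

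Worked line for ICC 0.05: DE = 1 + 4.09 × 0.05 = 1.204; V = 2.204 / 2 = 1.102; r = 1.050; 1.96 / 1.050 = 1.867; type I error = 6.2%.

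**5. Upper case: full groups of six analysed.** DE is 1.10 / 1.25 / 1.50 at ICC 0.02 / 0.05 / 0.10. Type I error is 5.6% / 6.5% / 8.0%, and one-sided power is 79% / 77% / 73%. A simulation of the naive t-test (7 groups of six against 42 independent controls, 40,000 runs) gave 6.6% and 8.1% at ICC 0.05 and 0.10, in line with the formula.

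**6. Sample size needed to keep 80% one-sided power.** Multiply 39 by V and round up. With m = 5.09 this gives 41 / 43 / 47 per arm, or 82 / 86 / 94 analysed in total. With full groups of six it gives 82 / 88 / 98. The plan has 78. These figures ignore the degrees of freedom lost with only about eight groups, so they are slightly optimistic.

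**The case against.** **The ICC may be small.** It is not given, and at zero there is no error. The text offers reasons to expect a low value: difficulty, rounds and progression are set for each person (Difficulty Level); the executive-function tasks are cylinder tasks described per participant; and the interactive tasks are a 10-minute warm-up that Table 2 lists under memory and working memory. This stands. It makes the concern conditional and keeps its size modest at an ICC of 0.05 or below.

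**Fixed groups, each with its own trainer.** A reader might infer both. The document states neither. Recalling five names over repeated rounds and following an identical schedule make stable membership plausible, no more. The nursing specialists are described as assigned to tasks at random, so trainers may cross groups.

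**Clustering in one arm only.** A reader might take this as established. It is a working assumption, because the control classes are of unstated size and it is not said whether the arms share them. If controls were clustered equally in groups of six, two-sided type I error would be 8.0% at ICC 0.05.

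**A power loss starting from 71%.** Two-sided power at 39 per arm is 71%, and one could be tempted to measure the damage from there. The gap between 80% and 71% comes from the unstated sidedness, which is a separate matter. Clustering accounts only for the falls shown from 81%.

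**A condensed article leaves such details to the SAP.** This would be a good answer if the article were silent. It names both the sample-size test and the primary analysis, and both assume independence, so this is a stated choice with a specific better alternative.

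**Conclusion.** The point holds in conditional form. The intervention is delivered in groups of six, while the stated sample size and primary analysis treat participants as independent. Whenever outcomes correlate positively within training groups, the standard error is understated and the test is anti-conservative.

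The effect is small at an ICC of 0.02 and becomes material near 0.10, where the true standard error is about 10% larger and a nominal 5% two-sided test runs at 7.4% (8.0% if full groups of six are analysed). These sizes rest on an assumed ICC, on stable groups, on no clustering in the control arm, and on 39 analysed of 46.

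The document does not support saying outright that the standard error is too small, since that needs an ICC above zero. The change is worth making but is not critical to the trial.

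**What to change.** 1. Record an identifier for training group and, where applicable, for trainer and health education class. State whether group membership is stable over the 10 weeks and how the control classes are formed.
2. Analyse the primary and secondary outcomes with a mixed model that has a random effect for training group in the training arm (partially nested), in addition to the within-person correlation over time. Extend the random effect to control classes if these are also fixed groups. Use small-sample degrees of freedom.
3. Report the estimated ICC, and give the power statement over the assumed range, for example 0.02 to 0.10.

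**Cost.** One or more recorded identifiers and a change of analysis wording. Intervals become slightly wider, and with about eight groups some degrees of freedom are lost even if the ICC proves near zero. The identifiers need to be recorded while training is under way, because a later correction may be impossible without them.

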**Methods:**

This program is a single-blinded, randomized, prospective clinical trial to test the effect of process-based multi-task cognitive training in older adults with MCI. Ninety participants with MCI will be recruited and randomly assigned to the cognitive training group (n=45) and the wait-list control group (n=45). The cognitive training group will receive 10 weeks of process-based multi-task cognitive training and health education twice a week, at 40~60 min per session. While the wait-list control group will only receive 10 weeks of health education during the research period. The effect is measured using the executive function, neuropsychological assessment performance and related brain activity assessed with electroencephalogram parameters (slowness and complexity of the EEG) at baseline, after 10 weeks of training, and a 3-month follow-up.

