#### Control Intervention

Participants in the control group are on the waiting list and will receive 10 weeks of health education classes twice a week, at 40~60 min per session. The wait-list group will access to attend the same after the group had completed a 3-month follow-up. The items of health education included the disease knowledge of MCI, physical activity, cognitive activities and social activity. Participants were reminded via smartphone to complete their training program if missing over 2 weeks.

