#### Study Procedure

Participants will be enrolled from the nearby community health service centre via open recruitment through paper flyers, online forums, and word-of-mouth. Participants who interested in this program will be invited for an in-person interview to complete a screening questionnaire in the community health service centre, including demographic characteristics, MMSE, MoCA, ADL, and Achromatopsia anomalous trichromatic test (AATT). A trained physician in community health service centre will invite the potential participants to undergo a physical examination and neurologic diagnosis of MCI. Participants who met the eligibility criteria will be assessed with a baseline assessment and then given the EEG evaluation in the 2 days preceding the start of the cognitive training.

After that, according to the random allocation sequence, participants will be randomly assigned to one of two groups with a targeted assignment ratio of 1:1. The random allocation sequence with a block size of four will be generated using a computer randomization list by an independent researcher assistant. The random allocation sequence is sealed in opaque envelopes by an assistant. The cognitive training group will receive cognitive intervention and health education, whereas the wait-list control group will only receive health education during the research period. During the 3 months follow up, the cognitive training group and wait-list control group will receive no interventions. Complete all outcome assessments, participants in the wait-list control group will be permitted to undergo the process-based multi-task cognitive training program. Although it was not initially the plan, the health education manual for mild cognitive impairment will be provided for participants who are not finishing the cognitive training or health education through various means, such as email, public platform, and short messaging service. All outcome measurements will be assessed at baseline, 10 weeks and 3 months follow up. Study assessments and timelines are illustrated in **Table 3**.

**Table 3 T3:** Summary of study assessments and timelines.

Time point	Measurement	Post-allocation					Mode of Administration
		Baseline	Training sessions	10 weeks assessments		Follow-up 3 months	
		T0		T1		T2	

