There are some limitations to the current study. First, the sample population in this study may not represent the overall characteristics of individuals with MCI. In this study, older adults with MCI who have colour blindness would be excluded. Thereby the result will be limited in informing the cognitive benefit generalisability. Second, considering the feasibility, we do not set up an active control group, which may compromise the statistical power. Third, the follow-up cognitive training in this study was limited to 3 months because we will provide compensable training for the wait-list control group after the follow-up period. Hence, conclusions regarding the longer follow-up effectiveness of the process-based multi-task cognitive training program could not be drawn. Future study should further explore the above research gaps.

In summary, our cognitive training program, implemented by socket cylinder and use of dynamic and hierarchical tasks (the difficulty increases as the participants’ performance improves), is easy to complete in older adults with MCI. This use dynamic and hierarchical tasks and multi-modal testing (paper-pencil, computer) will not only provide reliable data on cognitive training and transfer effects but also assure compliance and motivation of participants. The training program is valid, and the effects of training can be sustained will play a vital role in the application of cognitive training in the elderly with MCI. If proven effective, the results of this protocol will be relevant to community health workers to adopt a more cost-effective and feasible cognitive training method for improving the cognitive status, executive function, psychomotor speed, and non-trained cognitive domains.

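### Giving both arms the same health education does not balance social contact, and the stated limitation names lost power where the real limit is attribution to the training process

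*Protocol article*

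**What the plan says.** The section Implementation of the Cognitive Training Program gives a reason for adding education to the training arm: "To balance the social-interaction effect, participants in the cognitive training group participated in the same health education program as the wait-list control group".

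Study Procedure sets out the two arms: "The cognitive training group will receive cognitive intervention and health education, whereas the wait-list control group will only receive health education during the research period". Study Design and Participants describes them the same way.

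On amounts, the implementation section specifies "60 min group training sessions (a small group of six participants) each given three times per week" and divides each session as follows: "The task of warm-up exercise lasting 10 min, practice in order and expanding training tasks lasting 50 min". The abstract gives a different schedule: "10 weeks of process-based multi-task cognitive training and health education twice a week, at 40~60 min per session". Under Control Intervention, the wait-list arm "will receive 10 weeks of health education classes twice a week, at 40~60 min per session".

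Among the limitations in the Discussion, the authors write that, for reasons of feasibility, "we do not set up an active control group, which may compromise the statistical power".

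**The concern.** Two statements do not fit the design.

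The first is the purpose given for the shared classes. A component given equally to both arms cancels out of the comparison. It does nothing to offset a further component given to one arm only. All the small-group training contact lies on one side.

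The second is the limitation. A less active comparator does not in itself cost power. If attention, contact or expectancy improve test performance at all, their absence from the control arm widens the difference. What suffers is the interpretation of that difference.

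This matters because the aims go beyond asking whether the package works. The Objective concerns the effect of process-based training on executive function. The secondary and tertiary aims concern transfer to untrained domains and the brain activity underlying the training. Statistical Considerations plans a mediation model with cognitive training as the mediator. Each of these invites a statement about the training process. A reader who takes the balance sentence at face value would think that social contact had been ruled out as an explanation. Blinding does not fill the gap: Outcome Measurement describes blinding of evaluators and training practitioners, which does not remove participants' own expectancy or the effect of extra contact.

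**Working it through.** The protocol states no total contact time, so there is no figure to reproduce. The totals follow from its schedules.

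**Inputs**
- Training, implementation section: 3 sessions a week, 60 min, 10 weeks.
- Training, abstract: 2 sessions a week, 40 to 60 min, 10 weeks.
- Education, Control Intervention: 2 classes a week, 40 to 60 min, 10 weeks. The training arm attends the same programme.

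**Is education extra to the training session?** Warm-up plus tasks take 10 + 50 = 60 min. That is the full session in the implementation section, so no time is left in it for education.

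**Formulas**
- Minutes = weeks × sessions per week × minutes per session.
- Ratio = (training + education) / education.

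**Education, both arms:** 10 × 2 × 40 = 800 min (13.3 h) to 10 × 2 × 60 = 1200 min (20 h).

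**Training, implementation section:** 10 × 3 × 60 = 1800 min (30 h).

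**Training, abstract:** 10 × 2 × 40 = 800 min to 10 × 2 × 60 = 1200 min.

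| Training schedule | Training (min) | Education (min) | Training-arm total (min) | Ratio to control |
|---|---|---|---|---|
| Implementation section, 40-min classes | 1800 | 800 | 2600 | 3.25 |
| Implementation section, 60-min classes | 1800 | 1200 | 3000 | 2.50 |
| Abstract, 60-min training, 40-min classes | 1200 | 800 | 2000 | 2.50 |
| Abstract, 40-min training, 40-min classes | 800 | 800 | 1600 | 2.00 |
| Abstract, 60-min training, 60-min classes | 1200 | 1200 | 2400 | 2.00 |
| Abstract, 40-min training, 60-min classes | 800 | 1200 | 2000 | 1.67 |

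The abstract rows assume that education is delivered separately from training. Under the implementation section, the training arm has 30 h of supervised contact that the control arm lacks.

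**The case against.** The case on the other side has several parts.

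- **Hours are not social interaction.** This stands. Most of each session is cylinder work at an individualised level. Only the 10-min warm-up is described as interactive. Over 20 to 30 sessions that is 200 to 300 min, or 3.3 to 5 h. Counting only this as extra social time, the ratio runs from (20 + 3.3)/20 = 1.17 to (13.3 + 5)/13.3 = 1.38. The article does not say how interactive the classes are, so the size of the social imbalance cannot be derived. Even so, the imbalance is not zero, and supervision, attention and expectancy apply to the whole session.
- **The warm-up games are training content.** This stands. Table 2 lists name recall and miming as tasks for memory and working memory. They belong to the package and should not be called extraneous. They also show that content and contact cannot be pulled apart in this design.
- **The sentence states a purpose, and the arms are openly described.** This is partly right. The article nowhere says that total contact is equal, and a comparison of training added to education with education alone is legitimate. But the stated purpose is one the measure cannot achieve, and nothing later corrects it.
- **The missing active control is disclosed.** It is, but with the wrong consequence attached.

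A reader might also infer stronger points that the documents do not support:

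- *That contact is at least doubled on every reading.* It is not: 40-min training with 60-min classes gives 1.67. The abstract could even be read as training and education sharing the same two weekly sessions, which gives about 1. The fully used 60 min in the implementation section speaks against that reading, but the two places already disagree on frequency.
- *That a definite share of the planning effect of 0.575 is due to contact.* The documents give no size for a contact effect. The planning value is itself presented alongside superiority to wait-list, so it may already include such effects.
- *That the trial is invalid.* The randomised contrast of the package with education alone remains valid in this respect.

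**Conclusion.** The point holds as a matter of claim and interpretation. The shared classes leave the training arm with roughly 1.7 to 3.25 times the supervised contact of the control arm: 2.5 to 3.25 on the implementation section's schedule and 1.7 to 2.5 on the abstract's. These figures assume full attendance and education delivered separately from training. They measure supervised time, not social interaction and not bias in the effect estimate.

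The conclusion does not depend on the exact ratio. It needs only that the training contact is additional and confined to one arm, which the arm definitions show. A positive result would support the package over education alone. It would not show that the training process, as distinct from the contact and expectancy that come with it, produced the change. No change to design, sample size or primary analysis follows, but what the trial may conclude does change.

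**What to change.** 1. **Implementation of the Cognitive Training Program:** delete the balance claim, or restate it to say that both arms receive the same education classes and that the group training contact is additional in one arm.
2. **Aims and Statistical Considerations:** state that the trial estimates the effect of group training with its extra contact, added to education, against education alone. Limit the conclusions to that package, including those on transfer and neural mechanism.
3. **Discussion, limitations:** replace the remark about power with the statement that, without an active control, an effect cannot be separated from extra contact, attention and expectancy.
4. **Schedules:** reconcile the training frequency and session length between the abstract and the implementation section, and say whether education is delivered in separate sessions. Which schedule is right is for the investigators to state.
5. **Optional:** report attended contact hours by arm. The article mentions a paper training record but no record of education attendance, so this may need a simple class log.

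Items 1 to 4 are wording only and need no new arm, participants or assessments. The cost is a narrower and less favourable stated conclusion.
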